### Statistical Analysis

Statistical analyses will be carried out on the basis of the intention-to-treat approach and therefore will include all randomized participants. We will analyze the extent of the missing data, explore patterns and determine the type of missing data (missing completely at random, missing at random, not missing at random). Missing values will be substituted using multiple imputations. Sensitivity analyses will be conducted for both the data sets with and without the imputed data.

We will use linear mixed models to analyze all continuous outcomes as a change from baseline to compare effects between the two groups and over the different measurement points. In case of a missing at random mechanism, we will conduct multilevel regression analyses, which are less sensitive to missing data. Multiple regression analyses allow us to include several predictors such as time of measurement or group allocation [55].

Furthermore, exploratory analyses will be conducted. One of these will examine the association between adherence and outcome, since a higher adherence has been shown to have a positive effect on outcome [56,57].

All analyses will be conducted using SPSS (IBM Corporation) and R (R Foundation for Statistical Computing).

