In recent years, various web-based treatment options for adjustment problems and disorders have been developed. One of them is Trastornos Adaptivos Online [23,24]. The guided program comprises psychoeducational elements, strategies from positive psychology, and techniques to manage negative emotions and improve problem solving. In addition to the program, participants receive short weekly therapist support via telephone. Trastornos Adaptivos Online was well received by both clinicians and patients in a pilot study [24]. The program is currently being tested for its effectiveness in an RCT [23].

A further web-based intervention for the treatment of adjustment disorders is the Brief Adjustment Disorder Intervention [25,26]. This program is unguided and consists of four modules, which the participants can process in a self-determined order. The program’s theoretical approach is mainly CBT-based but also contains elements of mindfulness as well as findings from research on stress and coping [27]. Preliminary results of an RCT indicate that participants who used the program at least once within a month showed a decrease in symptoms of adjustment disorders and an increase in psychological well-being. However, there was a very high dropout rate, which is mentioned as the study’s most prominent limitation [26]. The authors tested the effects of additional therapist support on the program’s effectiveness. The additional support did not contribute significantly to the study’s outcomes [26]. This supports previous findings by Maercker et al [28] that web-based self-help interventions may be a promising treatment option for adjustment problems and further indicates that such interventions do not necessarily need scheduled guidance from a specialist.

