Another unguided web-based program for adjustment problems is ZIEL (German acronym: Zurück Ins Eigene Leben; “back to your own life”) [29]. The ZIEL program comprises different evidence-based techniques from treatments for depression, anxiety disorders, and post-traumatic stress disorders. ZIEL consists of 5 sections which participants can work through freely and as needed over a course of 4 weeks. In an RCT, the participants of both the experimental and the control group showed an improvement in the severity of symptoms of adjustment problems. The intervention group, however, showed a significantly greater improvement in terms of depressive symptoms and quality of life. However, the authors of ZIEL also report challenges with a high dropout rate and suggest different measures to address this. One of these suggestions is to focus on certain subgroups of people with adjustment problems or on certain triggers of adjustment problems. This, in turn, would allow for a more tailored response to the needs of the users, thereby creating a better user-program fit and greater relevance for the users [29].

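### The plan sets out to identify the missing-data mechanism, which observed data cannot do, and its stated sensitivity check does not probe the missing-at-random assumption

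*Protocol article*

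**What the plan says.** Everything on missing data is in the Statistical Analysis section of the protocol article.

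- After looking at how much is missing and in what pattern, the team will "determine the type of missing data (missing completely at random, missing at random, not missing at random"). The mechanism is thus to be read from the trial's own data.
- Imputation is stated without condition: "Missing values will be substituted using multiple imputations". The imputation model is not described.
- The sensitivity check reads: "Sensitivity analyses will be conducted for both the data sets with and without the imputed data".
- The main model is also unconditional: "We will use linear mixed models to analyze all continuous outcomes as a change from baseline".
- One sentence is conditional on the mechanism: "In case of a missing at random mechanism, we will conduct multilevel regression analyses, which are less sensitive to missing data". No analysis is attached to the other two possible results of the mechanism step.

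Two other places bear on the point. Under Web-based Psychological Interventions, the article reports of one comparable programme that "there was a very high dropout rate", and of the programme whose results feed the power calculation that "the authors of ZIEL also report challenges with a high dropout rate". Neither statement comes with a figure. Under Study Design, people who drop out are still to be asked for the remaining assessments, and there are measurements at weeks 4 and 8 before the week-12 post-measurement.

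**The concern.** MAR and not missing at random differ only in whether missingness depends on values that were not seen, given those that were. The observed data hold no information on that difference. A test or pattern analysis can give evidence against MCAR, but nothing in the data can certify MAR. A team that follows the text will have to declare a result it has not established, and one sentence of the analysis is tied to that declaration.

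The second part concerns what a reader will take from the sensitivity analysis. Results with and without imputation will often agree. That agreement is likely to be reported as robustness to dropout, although both analyses would normally share the assumption in question. The article itself expects this field to have high dropout, and the effect it plans for is as small as d=0.2. A modest unexamined bias would therefore matter to the conclusion.

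**Working it through.** **The plan's own figures.** The plan gives no figure for missing data. The yardstick is the effect size in the Power section: d=0.2 to 0.35, alpha .05, power 0.80, r=0.4, giving 238 and 80 participants and a target of 240. Both totals reproduce with the repeated-measures within-between interaction test for 2 groups and 2 measurements, with f=d/2 and noncentrality λ = f²·N·m/(1−r):

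- d=0.2: λ = 0.01×238×2/0.6 = 7.93, N=238
- d=0.35: λ = 0.030625×80×2/0.6 = 8.17, N=80

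Power at N=240 and d=0.2 is 0.804. The present point does not depend on these totals. Below, d is taken at face value as the between-arm difference in SD units.

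**Can the mechanism be determined?** No arithmetic is needed. Of the three categories listed, only MCAR has consequences that can be checked in the observed data. MAR versus not missing at random cannot be checked.

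**Does the conditional sentence change the analysis?** The linear mixed model is planned whatever the mechanism, and so is multiple imputation. A multilevel regression with time and group as predictors belongs to the same model class. The condition therefore adds no new analysis.

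**What does the sensitivity check test?** Standard multiple imputation assumes MAR. A likelihood mixed model on the unimputed data also assumes MAR. A complete-case version generally needs stricter conditions. None of the three relaxes MAR.

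**Size of what stays hidden.** Let p be the share of an arm with week-12 data missing, and δ how much worse (in SD) those participants truly are than MAR predicts. A MAR analysis misstates that arm's mean by p·δ, so

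bias = p(SelFIT)·δ(SelFIT) − p(CAU)·δ(CAU),

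where a positive value overstates the benefit of SelFIT. All rates and shifts below are assumed. With a shift in the SelFIT arm only:

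| Missing | Shift | Bias (SD) | Share of d=0.2 | Share of d=0.35 |
|---|---|---|---|---|
| 30% | 0.2 | 0.06 | 30% | 17% |
| 40% | 0.2 | 0.08 | 40% | 23% |
| 30% | 0.3 | 0.09 | 45% | 26% |
| 40% | 0.3 | 0.12 | 60% | 34% |

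The same formula gives other answers under other assumptions. With 30% missing and a 0.2 SD shift in both arms, the bias is 0.06 − 0.06 = 0. With that shift in the control arm only, it is −0.06 SD, against SelFIT.

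**Simulation check** (120 per arm, r=0.4, true effect zero, 4,000 runs, baseline-adjusted model on observed week-12 data, intermediate scores not used):

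- 40% vs 20% missing, no shift (missingness depends on arm only, a special case of MAR): bias 0.004, type I error 5.4%.
- 30% missing in each arm, 0.5 SD shift in both: bias 0.001, type I error 5.1%.
- 40% vs 20% missing, 0.3 SD shift in the SelFIT arm only: bias 0.118 in favour of SelFIT (formula 0.12), type I error 12.8%.

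**Tipping point.** The SelFIT-only shift that would account for the whole of d=0.2 is 0.2/p: 1.0, 0.67, 0.50 and 0.40 SD at 20, 30, 40 and 50% missing. A delta-adjusted analysis would report this quantity. The planned comparison cannot.

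**The case against.** The strongest reply is that this is a fault of wording with little consequence, and that a condensed article leaves the rest to an analysis plan that is not shown. Several parts of that reply stand.

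- *A reader might infer that the mechanism step selects the primary model.* The text does not support this. Multiple imputation and the mixed model are both planned unconditionally, and only one sentence is conditional.
- *A reader might infer that unequal dropout between the arms is itself the danger.* It is not. Under MAR, 40% against 20% missing produced no bias. The exposure needs dropout that depends on unseen outcomes and does so differently by arm.
- *A reader might infer that the bias favours SelFIT,* because users who are not helped may leave while controls wait for access. The documents report no reasons for dropout and no split by arm. Users who recover quickly might stop answering, or controls who are doing badly might leave, and either would bias against SelFIT.
- *Stopping the programme is not the same as missing data.* Dropouts are still asked for later assessments, and a poor course already visible at weeks 4 and 8 is information that a MAR model can use. This reduces the exposure but does not remove it, because being asked does not guarantee an answer.
- *The MAR basis of the imputation is inferred.* The article does not describe the imputation model or say whether the unimputed analysis is likelihood-based or complete-case.
- *The absence of a not-missing-at-random analysis is not in itself a finding,* since a separate analysis plan could contain one.

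The reply does not rescue the two things the article does state. No later document can make the mechanism determinable from the data. And the sensitivity analysis that the article chose to name does not, in its standard form, address the assumption that matters.

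**Conclusion.** The point holds in a limited form. The article commits to a determination that observed data cannot supply, and it attaches a redundant conditional analysis to it. The sensitivity check it names would not show robustness to outcome-dependent dropout that differs by arm, provided the imputation and the mixed model both rest on MAR, as is usual.

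The possible size is illustrative, because the documents give neither dropout rates nor shifts. Under the assumed 30–40% missing and a 0.2–0.3 SD shift confined to one arm, the estimate moves by 0.06–0.12 SD. The sign is unknown, and the bias vanishes when dropout times shift is equal in the two arms. Against the lower planned effect of d=0.2 this is large enough to deserve a proper check. It is not evidence that the trial's result will be biased.

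**What to change.** In the Statistical Analysis section:

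1. Delete the step that determines the mechanism and the sentence conditional on MAR. Describing the extent and pattern of missing data by arm can stay.
2. State one likelihood-based linear mixed model on all randomised participants, with MAR as its declared assumption, as the primary analysis.
3. Keep the comparison with and without imputation only as a secondary check, and do not present it as a test of MAR.
4. Add delta-adjusted multiple imputation as a tipping-point analysis, with shifts allowed to differ by arm and in either direction, and report the shift at which the week-12 conclusion changes. Reference-based imputation, with missing SelFIT participants taken to follow the control arm, is an optional addition.

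The cost is a few sentences and one extra analysis in R, which is already planned software. No new data are needed.

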#### Randomization

After receipt of the informed consent and the initial screening, participants are randomized equally (1:1 ratio) into the treatment or the control group. Randomization is stratified by the point value that participants score on the questionnaire used as the primary outcome measure (12-16 points vs ≥17 points) in order to make the two groups comparable regarding their symptom expression on this measure. This is done with a computerized random number generator and randomly permuted block sizes using Randomization.com [31]. Randomization within each stratum uses a 1:1 ratio as well. The allocation schedule is generated by a researcher not involved in the research process and is unknown to the investigators.

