#### Accident-Related Measures

Regarding the accident, we ask for a short description of the event, the time that has passed since, and its subjectively perceived severity.

Pain due to the accident is assessed by the Brief Pain Inventory [37], which consists of 15 items. After the question of whether there is any pain that exceeds the normal levels expected in everyday life, participants have to indicate where the pain is located and how severe the limitations in various areas of life are due to the pain. We also assess the participants’ own perception of their physical attractiveness. Physical attractiveness is a very influential informational cue that is used frequently and consistently [38,39]. It has been shown to play an important role in how a person is perceived and responded to in many areas of life [38]. This includes health and psychological well-being. Bordieri et al [40] found that physical attractiveness influenced how others make attributions concerning the cause and prognosis of someone’s disability. Physical attractiveness was also linked to self-esteem [40]. Among the possible consequences of an accident is skin scarring. In most cases, this is perceived as unattractive [41]. Brown et al [41] found that skin scars impact a person’s acceptability to others as well as themselves and also have an effect on social functioning and emotional well-being. Thus, participants in this study are asked to rate their own physical attractiveness compared to that of other people their age. They also have to indicate how often they think about being rated by others in terms of physical attractiveness. Furthermore, the participants assess if and how much their own perception of their physical attractiveness has changed since the accident.

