### Power

In order to specify the sample size needed for the planned analyses, we conducted a power analysis based on a probability level of .05 and a power of 0.80 using G*Power (Heinrich-Heine-Universität Düsseldorf) [54]. To test the program’s efficacy compared to the control group, we expect small-to-moderate effect sizes between *d*=0.2 and *d*=0.35 as well as a correlation between the groups of *r*=0.4. Those estimates are based on the results of previous web-based interventions for adjustment problems [29].

The a priori power analyses yielded a necessary sample size of 80 (for *d*=0.35) to 238 (for *d*=0.2) participants in total for this analysis. Since the program does not include weekly guidance but rather guidance on demand, we expect slightly smaller effect sizes. Based on these calculations and assumptions we decided to target a sample size of N=240 participants.

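### Change from baseline is fixed as the response and no baseline-score or stratum covariate is named; at the plan's r=0.4, baseline adjustment would save up to 30% of the variance

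*Protocol article*

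**What the plan says.** The Statistical Analysis section says the trial will use "linear mixed models to analyze all continuous outcomes as a change from baseline", comparing the two groups over the measurement points. The only predictors mentioned are measurement time and group, and they are given as examples. Neither the baseline score nor the randomisation stratum is named as a covariate, and neither is ruled out.

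The Randomization section states: "Randomization is stratified by the point value that participants score on the questionnaire used as the primary outcome measure (12-16 points vs ≥17 points"). The baseline score on the primary measure therefore already has a role in the design.

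The Power section describes a calculation for the planned analyses, "based on a probability level of .05 and a power of 0.80", with "small-to-moderate effect sizes between *d*=0.2 and *d*=0.35" and "a correlation between the groups of *r*=0.4". It reports a "necessary sample size of 80 (for *d*=0.35) to 238 (for *d*=0.2) participants in total", and the target is N=240.

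**The concern.** Subtracting the baseline forces a slope of 1 on it. When the pre-post correlation is modest, the best-fitting slope is well below 1, and the subtraction carries baseline noise into the outcome. A model that estimates the slope removes that noise using data the trial collects anyway.

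The stratum raises a related issue. The DASS-21 has 21 items scored 0 to 3, so it runs to 63, and the upper stratum spans 17 to 63. Two strata balance baseline only coarsely. If a stratification factor that predicts the outcome is left out of the model, the reported standard errors stay larger than the design warrants.

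What is at stake is the width of the confidence interval for the main comparison, and for every other continuous outcome analysed the same way.

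**Working it through.** **1. Reproduce the plan's sample size.** Inputs from the Power section: alpha 0.05, power 0.80, d=0.2 and 0.35, r=0.4. From the Randomization section: two groups, 1:1. Not stated, so assumed: two measurements and effect size f=d/2. For the group-by-time interaction, λ = f²·N·m/(1−r) with m=2 and df (1, N−2):

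- d=0.2: λ = 0.1²×238×2/0.6 = 7.93; power 0.801 at N=238.
- d=0.35: λ = 0.175²×80×2/0.6 = 8.17; power 0.806 at N=80.

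Both stated figures are matched exactly. The alternatives tried do not match. For d=0.2, the interaction with 3, 4 or 6 measurements gives 196, 166 or 130. The between-group test with two measurements gives 552. A follow-up-only comparison gives 786 two-sided or 620 one-sided.

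Two things follow. First, r=0.4 is labelled as a correlation between groups but works in the calculation as the correlation between two repeated measurements. Second, with two time points the interaction test is the t test on the unadjusted change score. Under the same effect convention, a baseline-adjusted analysis would have needed about 238×0.84/1.20 = 167, not 238.

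**2. Compare precision at one follow-up visit.** Variance per participant in units of the outcome variance, with equal SDs at both times (assumed) and r=0.4; the SE of the group difference uses 120 per arm, √(variance×2/120):

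| Analysis | Formula | Variance | SE | Simulated SE (5,000 runs) |
|---|---|---|---|---|
| Unadjusted change | 2(1−r) | 1.20 | 0.141 | 0.142 |
| Follow-up only | 1 | 1.00 | 0.129 | 0.130 |
| Baseline-adjusted | 1−r² | 0.84 | 0.118 | 0.119 |

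The saving from adjustment is 1−0.84/1.20 = 30% of the variance, and 1−√0.70 = 16% of the SE.

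**3. Vary the assumptions.**

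- *Correlation.* At equal SDs the saving is 1−(1−r²)/[2(1−r)] = (1−r)/2. That is 25%, 20% and 15% at r=0.5, 0.6 and 0.7.
- *SD ratio.* If the baseline SD is k times the follow-up SD, the change variance is 1+k²−2rk. It exceeds the adjusted variance by (k−r)², which is never negative. At r=0.4, k=0.8 gives 1.00 (saving 16%) and k=0.7 gives 0.93 (saving 10%). The documents give no SDs, so these k values are assumptions.
- *Balance from stratification.* If a share q of the baseline variance is balanced by design, the true change-score variance is (1−r)²(1−q)+(1−r²). For assumed q of 0.30 to 0.64 this is 1.09 to 0.97, and the saving against 0.84 is 23% to 13%.
- *Several visits.* For the mean of three post-baseline measures with common correlation 0.4, the variances are 0.80 (change), 0.60 (follow-up only) and 0.44 (adjusted). The order is the same.

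**4. Check whether the response itself matters.** With the baseline score as a covariate, modelling change or modelling the follow-up score gave identical estimates and SEs in the simulation. Only the baseline coefficient differs, by 1.

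**The case against.** The strongest objection is that absence of adjustment is read from silence. The predictor list is open, the article condenses a fuller protocol, and an analysis plan that is not shown may name the covariates. If it includes baseline, the loss disappears, because change from baseline is then harmless as a response. This stands as far as it goes: the article does not say the model is unadjusted. But the choice of response is stated, and the sample size matches an unadjusted change-score test, so the text as written points that way.

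Three stronger readings are tempting, and the documents do not support them.

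- *That the change score is worse than ignoring baseline altogether.* This is true at r=0.4 with equal SDs (1.20 against 1.00), but it needs r<0.5. At r=0.6 the change score has 0.80 and beats follow-up alone. Entry requires a minimum score on this same scale, which may restrict baseline spread; at k=0.8 the two tie.
- *That chance baseline imbalance biases the comparison.* Allocation is randomised, so imbalance averages to zero. Its effect is already counted in the variances above.
- *That the trial is short of power.* That depends on how d was turned into the effect size for the power calculation, which is a separate question. Nothing here relies on it.

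**Conclusion.** The point holds as one of precision. Change from baseline is fixed as the response, and neither the baseline score nor the stratum is named as a covariate. The article's own sample sizes match an unadjusted change-score test. At r=0.4 and equal SDs, baseline adjustment saves up to 30% of the variance and 16% of the SE at a single visit. Under the departures tried, the saving falls to between about 10% and 25%.

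The size rests on three assumptions: that r=0.4 is the pre-post correlation (supported by the reproduction, not by its label), that the two SDs are equal, and that stratification takes up little of the baseline variance. The direction does not depend on r or the SD ratio, since the adjusted variance is never the larger. The change should be made, but it does not call the validity of the comparison into question.

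**What to change.** Add one sentence to the analysis section. The mixed model for each continuous outcome includes that outcome's continuous baseline score, a baseline-by-visit term, and the randomisation stratum (12-16 versus 17 and above on the DASS-21) as covariates. Once baseline is in the model, the response may remain change from baseline or be the follow-up score.

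The baseline scores and the stratum are already recorded, so no new data are needed. If the unseen analysis plan already contains these terms, the article only needs to say so. The sentence should be settled before outcome data are examined by group.

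Time since the accident is also recorded ("we ask for a short description of the event, the time that has passed since, and its subjectively perceived severity"). Nothing in the article shows that it predicts outcome, so adding it as a covariate is optional and not part of this fix.
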